### 1.6 Study endpoints

• ULT-EEG is analyzed to assess potential electrophysiological biomarkers resembling sleepiness or sleep pressure, such as wake–sleep transition rate, timing, and daytime sleep patterns in the micro and macro perspective or vigilance state classification. This will be assessed through automated microsleep detection and automated sleep-stage classification methods. Using concomitant PSG and ULT-EEG, we will identify the markers of stage transition from awake to dozing/light sleep in the SubQ recording. We will do this both according to AASM criteria and in shorter segments of EEG. From this template, we will use machine learning (ML) techniques to train a classifier to detect those short transitions in the ULT-EEG recording with different levels of sensitivity and specificity.

• The correlation between ULT-EEG-derived biomarker candidates and well-known sleepiness metrics, such as the mean sleep latency and EMA collected reaction time, and ESS and KSS scores, as well as patient reports of episodes of daytime sleeping or dozing off (nap diary). From the timestamps on PVT prompts to patients, we will identify segments of interest in the ULT-EEG recording to document changes in EEG-related signs of reduced vigilance. We will use this to validate the responses on the clinical scales given by patients.

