#### 2.4.6 Sleep and nap diary

During the 12-week study, the participant will fill in daily “sleep and nap diary”, subjective registration of napping patterns, and sudden sleep episodes. At 08:00, the participant will receive a notification to fill in a sleep survey, asking, “What time did you get out of bed today?” and “When did you go to sleep last night?” At 21:00, the participant will receive a notification to register sleep or nap episodes that might have occurred during the day, asking, “Have you been sleeping during the day?” If yes, an additional question is posed: “How long have you been sleeping during the day?” For every daytime sleep episode, the participant is asked to determine the type of nap: “I consciously took a nap because I felt the need to”, “I fell asleep without the intention to”, and “I registered I had fallen asleep when I suddenly woke up”. The subjects are asked to press the event button of the 24/7 SubQ device one time if they experience waking up from an unintended nap during the daytime. Likewise, the subjects are asked to press the event button twice before taking a planned nap during the day. This records an event in the EEG signal.

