### 3.1 Discrepancies between subjective sleepiness, behavioral factors, and dozing-off phenomena

Making objective measures and quantifying the multifaceted phenomenon of sleepiness has been referred to as the holy grail of sleep medicine (Bliwise, 2001). This is probably because several factors, such as physiological, psycho/social, and behavioral factors, influence sleepiness. We look into the differences between dozing off and reporting feeling sleepy, as we find that these concepts are not interchangeable (Thorarinsdottir et al., 2019). Being capable of feeling sleepiness is suggested as a protection mechanism to help restrain risk-related activities, such as car driving, because of the potential reduced alertness (Cai et al., 2021). This mechanism is likely altered differently across the different origins of sleepiness, such as Parkinson's disease, narcolepsy, or OSA (Möller et al., 2009). For example, “blank spells” or sudden onset sleep without prior sleepiness perception have been described for Parkinson's patients but not for OSA patients (Hobson et al., 2002).

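### The nap diary's opening question asks only about sleeping although the diary is meant to report dozing off too, and two of its three nap types overlap

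*Protocol article*

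**What the plan says.** Section 1.6 (Study endpoints) correlates the EEG biomarker candidates with mean sleep latency, reaction time, ESS and KSS, and also with "patient reports of episodes of daytime sleeping or dozing off (nap diary". Section 1.4 (Objectives) likewise gives the diary the task of recording both falling asleep and dozing off.

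Section 2.4.6 describes the diary as "subjective registration of napping patterns, and sudden sleep episodes". A notification at 21:00 asks the participant to "register sleep or nap episodes that might have occurred during the day". The item printed is "Have you been sleeping during the day?” If yes, an additional question is posed", and that further question concerns duration. Each daytime sleep episode is then classified as one of three types: "I consciously took a nap because I felt the need to", or one of the pair "I fell asleep without the intention to”, and “I registered I had fallen asleep when I suddenly woke up". The section gives no rule for choosing between the last two and does not say whether more than one may be ticked.

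The implant recorder's event button is a second way of marking episodes. Section 2.4.6 asks for one press on waking from an unintended nap and two presses before a planned one. Section 2.4.1 (The implantation) asks for a double tap at lights-out and also for unintentional daytime sleep.

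**The concern.** There are two separate weaknesses in the printed items.

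- **Opening question.** The endpoint names sleeping and dozing off, but the question names only sleeping. The article itself treats the two as different terms when it describes the ESS in Section 1.1. On the EEG side, Section 1.6 aims the classifier at the transition from wakefulness into dozing or light sleep, including segments shorter than the standard scoring epoch. The biomarker is thus aimed at brief events that the diary may not elicit. A doze that goes unreported on the diary side pulls down the agreement between the two measures, even if the EEG detection is right.
- **Nap types.** If one episode can properly be entered under either of two options, the counts under each depend partly on how a participant reads the list. Any comparison between those two counts, including before versus during CPAP, would then have no clear meaning.

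**Working it through.** The documents state no figure that depends on the diary wording. The sample size in Section 2.8 is built on the ESS. The check is therefore a comparison of the texts, plus a count of exposure.

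**1. Target against item.**

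| Place | What is covered |
|---|---|
| Section 1.4 | falling asleep, dozing off |
| Section 1.6 | daytime sleeping, dozing off |
| Section 2.4.6, purpose of the 21:00 notification | sleep or nap episodes |
| Section 2.4.6, opening question | sleeping |

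Dozing drops out between the endpoint and the item.

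**2. Size of the loss.** Let d be the share of target episodes that are brief dozes, and u the share of those dozes that participants do not regard as sleep and so do not report. The share of target episodes captured is 1 − d × u. The documents give neither d nor u. With both free between 0 and 1, capture runs from 1 − 1 × 1 = 0% to 1 − 0 = 100%. Assuming u between 30% and 70% gives 70% to 30% of dozes captured, which only restates the assumption and says nothing about all episodes unless d is known.

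**3. Exposure.** 12 weeks × 7 days = 84 evening entries per participant, and 84 × 15 participants = 1,260. This is the maximum number of entries using the wording with no missing data. It is not a count of wrong entries.

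**4. Exclusivity of the nap types.**

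- Type 1 is a deliberate nap.
- Type 2 is defined by absence of intention.
- Type 3 is defined by finding out on waking.

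Types 2 and 3 use different criteria, and an unintended episode discovered on waking meets both. Type 1 stays separate from both. So type 1 against types 2 and 3 combined is well defined, while type 2 against type 3 is not.

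**5. The event button as a backup.** Under Section 2.4.6 a double press marks a planned nap. Under Section 2.4.1 it marks lights-out or unintentional daytime sleep. Read together, a daytime double press can mean a planned or an unintended episode. The button therefore cannot settle what the diary leaves open until the two sections agree.

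**The case against.** The case on the other side has real force.

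- **The loss is not shown.** Two of the three nap types describe unintended sleep, so the diary clearly looks for it, and a participant who noticed dozing may well answer yes. The event button does not depend on the 21:00 question. This stands: under-reporting is a risk of unknown size.
- **The diary is not the reference standard.** A reader might infer that EEG-detected dozes will be counted as false positives because the diary missed them. The documents do not support this. The classifier template comes from concomitant PSG and subcutaneous EEG (Section 1.6), and automatic sleep/wake classification is validated against manually scored PSG (Section 1.4). The diary is a correlate. Microsleeps, which Section 2.9.3 puts at under 15 s, would not become reliably reportable under any wording.
- **No stated analysis uses the split between types 2 and 3.** A reader might infer that drift between them would be mistaken for a CPAP effect. Sections 1.4, 1.6 and 2.7 plan no such comparison, so this harm is hypothetical.
- **Type 3 may be about awareness.** A reader might take it as the item for sleep without warning, the more so because the diary is said to register sudden sleep. But its wording describes sudden waking, and nothing says it was meant to capture absence of prior sleepiness. Section 3.1 adds that "blank spells” or sudden onset sleep without prior sleepiness perception have been described for Parkinson's patients but not for OSA patients", which weakens the case for a dedicated item.
- **The printed items may be translations** of what the app shows, and the participant instructions are not visible.

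These arguments limit the size of the point. They do not remove the mismatch between endpoint and question or the overlap between types, both of which are visible in the printed text.

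**Conclusion.** The concern holds in limited form. The opening question is narrower than the report that Sections 1.4 and 1.6 assign to the diary, so brief dozes may be under-reported and the diary-EEG correlation weakened by an amount that cannot be estimated from the documents. The division between the two unintended nap types cannot be interpreted. Planned versus unintended sleep is unaffected by the overlap.

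It would go too far to say that dozing and sudden sleep are missed, or that the endpoint rests on these items. Unintended sleep can still be reported after a yes, and the endpoint lists the diary beside mean sleep latency, reaction time, ESS and KSS. The severity is minor to moderate. The conclusion assumes that the app shows wording equivalent to the printed English.

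**What to change.** 1. Check the wording, the option rules and the participant instructions actually used in the app. If dozing is already named there, correct the article and stop at step 3.
2. Otherwise, for participants not yet started, name dozing in the opening question, for example: *Did you sleep or doze off, even briefly, during the day?*
3. Analyse nap types 2 and 3 pooled as unintended sleep, for all participants, and do not interpret the split between them.
4. Reconcile the event-button instructions in Sections 2.4.1 and 2.4.6, so that a press pattern has one meaning. For recordings already made, establish which instruction each participant was given before using the marks.

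The cost is a text edit in the smartphone survey and one sentence in the analysis. The downside is that diary entries must be analysed by wording version if some participants used the old text. Limiting the new wording to participants not yet started keeps each person's before-and-after-CPAP comparison on a single version.

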### 2.5 Inclusion criteria

For a subject to be eligible, all inclusion criteria must be answered “yes”:

Age ≥18 years.Must be diagnosed with severe OSA (AHI score >30) and have not yet started any form of positive airway pressure treatment.ESS score above 10 at the time of inclusion.

### 2.6 Exclusion criteria

For a subject to be eligible, participants must answer “no” to all exclusion criteria:

Known severe neurological or psychiatric diseases.Known congestive heart failure, chronic renal failure, liver failure, malignancy, or severe pulmonary disease.Considerable use of alcohol.Medication judged by the investigator to influence sleep/wake regulation to such a degree that data quality will be compromised.Has cochlear implants.Involved in therapies with medical devices that deliver electrical energy into the area around the implant.Is at high risk of surgical complications, such as active systemic infection and hemorrhagic disease.Are unable (i.e., mentally or physically impaired patient) or do not have the necessary assistance to operate the device system properly.Has an infection at the site of device implantation.Operates magnetic resonance imaging scanners.Has a profession/hobby that includes activity imposing extreme pressure variations (e.g., diving or parachute jumping). Nota Bene (NB): diving/snorkeling is allowed to a 5-meter depth.Has a profession/hobby that includes activity imposing an unacceptable risk for trauma against the device or the site of implantation (e.g., martial arts or boxing).Other known diseases or conditions judged by the investigator to influence sleep to such a degree that data quality will be compromised.Incapable, judged by the investigator, of understanding the participant instructions or is not capable of carrying through with the investigation.Pregnancy or intention to become pregnant within the next 12 months.

### 2.7 Statistical considerations

As this is an exploratory and observational study, a similar exploratory approach will be used for statistical analysis. Therefore, the statistical analysis plan is not fixed, and the choice of statistical methods will be data-dependent. Data will be scrutinized for potential biomarkers related to EDS. The data analysis will be conducted with the DTU. The preliminary approach is based on classical time domain and frequency domain analysis. Artificial intelligence and ML will be used when applicable.

We aim to identify sleep/wake regulation patterns through several methodological approaches like VIGALL, microsleep detection, and macro-sleep/napping detection and correlate these to well-established metrics of sleepiness, such as mean sleep latency, reaction time, subjective sleepiness scores, and previous night's metrics of sleep quality.

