### 1.4 Objectives

This project aims to develop new sleepiness biomarkers using ultra-long-term at-home EEG monitoring as a novel, new data type. We will conduct a clinical study exploring electrophysiological sleep/wake transition phenomena in a population with OSA and EDS by making ultra-long-term subcutaneous EEG recordings in subjects' real-life conditions before treatment and as they start treatment.

We follow an explorative objective and an experimental one. We aim to validate our explorative findings in an experimental setting.

Our *explorative* objective is to scrutinize subcutaneous ULT-EEG for potential biomarkers predicting sleepiness in OSA patients. Determining daytime wake-to-sleep transition rate, microsleep episodes, and macro-sleep episodes, alongside the duration and patterns of these events. In addition, vigilance determination of the odds ratio product (ORP) (Younes, 2023) or Vigilance Algorithm Leipzig (VIGALL) (Olbrich et al., 2015) can be assessed. Our explorative findings will be correlated and preliminarily validated against the well-established sleepiness metrics and questionnaires, the MSLT, the ESS, the Karolinska Sleepiness Scale (KSS), and the Psychomotor Vigilance Task (PVT) test, as well as patients' experiences of falling asleep or dozing off in the form of a “sleep and nap diary”. Any potential sleepiness biomarker derived from this study will be available for future confirmatory trials.

Our *experimental* objective is to determine the effects of CPAP treatment on sleep quality, quantity, and timing from the day-to-day perspective that ULT-EEG provides. Furthermore, the experimental design enables us to clinically validate the exploratively deduced sleepiness biomarker candidates through comparisons before and after the intervention of CPAP treatment conditions. Previous studies on CPAP's effect on reducing sleepiness have shown a dose-dependent configuration with CPAP usage. ESS scores are typically reduced by 4.75 points (Patel et al., 2003). We expect relevant biomarker candidates to follow similar patterns when CPAP is introduced in a population with severe OSA and EDS.

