Our *secondary objective* is to validate automatic sleep/wake classification based on two-channel subcutaneous EEG against golden standard manually scored polysomnography in patients with severe OSA. Additionally, we explore using ecological momentary assessment (EMA) methods to record excessive daytime sleepiness in patients with OSA and collect passive sensor data from participants' smartphones to assess physical activity.

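### The biomarker search is open and data-dependent, yet the CPAP comparison in the same 15 patients is said to validate its results, and nothing keeps CPAP-phase data out of the selection

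*Protocol article*

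**What the plan says.** **Search.** Section 2.7 (Statistical considerations) states that "the statistical analysis plan is not fixed, and the choice of statistical methods will be data-dependent" and that "Data will be scrutinized for potential biomarkers related to EDS". It names several approaches (VIGALL, microsleep, macro-sleep or napping). Sections 1.4 and 1.6 add wake–sleep transition rate and ORP. No section limits the number of candidates.

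**Data.** Section 1.4 (Objectives) describes the exploration as making "ultra-long-term subcutaneous EEG recordings in subjects' real-life conditions before treatment and as they start treatment". Section 1.5 gives one cohort of 15 patients.

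**Validation.** For the established sleepiness measures, Section 1.4 is guarded: "Our explorative findings will be correlated and preliminarily validated against the well-established sleepiness metrics and questionnaires". For the experimental objective it is not: the design is meant to "clinically validate the exploratively deduced sleepiness biomarker candidates through comparisons before and after the intervention of CPAP treatment conditions". The same paragraph expects relevant candidates to behave under CPAP as the ESS does.

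**Trained models.** Section 1.6 uses concomitant polysomnography (PSG) and subcutaneous EEG as a template from which "we will use machine learning (ML) techniques to train a classifier to detect those short transitions", at several levels of sensitivity and specificity. The secondary objective in Section 1.4 is to "validate automatic sleep/wake classification based on two-channel subcutaneous EEG against golden standard manually scored polysomnography". Section 2.9.2 plans to fine-tune existing sleep-scoring models.

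**The concern.** An open search is proper in an exploratory study. The difficulty is the step from search to validation. If methods, features and thresholds may be chosen after all the data have been seen, the CPAP contrast can influence which candidate is put forward, and the same contrast is then offered as evidence for it. A result obtained in that way is biased towards success by an unknown amount.

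The experimental objective is at stake. A marker reported as clinically validated in 15 patients could go into later work on treatment monitoring or fitness to drive, both named in Section 1.2, with an optimistic effect size. Section 2.7 itself says that the plan is not fixed, so this point cannot be assumed settled in an analysis plan that is not shown.

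**Working it through.** **1. The plan's own figure.** Section 2.8 gives 12 participants for 95% power, using a repeated-measures within-factor ANOVA on the ESS.
- Inputs from Section 2.8: effect size 0.3, read as Cohen's f; 6 + 6 weekly scores + 1 at inclusion = 13 measurements.
- Assumed, because not stated: alpha 0.05, correlation 0.5, sphericity, one group.
- Noncentrality: λ = f²·N·m/(1−ρ) = 0.09 × 12 × 13 / 0.5 = 28.08. Degrees of freedom: 12 and 11 × 12 = 132.
- Power = 0.951, so N = 12 is reproduced. With 12 measurements, power at N = 12 is 0.938 and N becomes 13.

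This calculation concerns the change in ESS only. It says nothing about the error rate of choosing among EEG candidates.

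**2. Illustration: best of K null candidates, n = 15.** The article gives no K, so K is an assumption. Each candidate has one value per patient and no true association, tested two-sided at 0.05.
- Critical correlation: |r| = t/√(13 + t²) with t = 2.160, which gives 0.514.
- Chance of at least one p<0.05 with independent candidates: 1 − 0.95^K. Simulation agrees.

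| K | Chance of at least one p<0.05 | Median best \|r\| |
|---|---|---|
| 1 | 5% | 0.19 |
| 5 | 23% | 0.41 |
| 10 | 40% | 0.49 |
| 20 | 64% | 0.55 |
| 50 | 92% | 0.62 |

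**3. The before/after contrast.** The same reasoning applies to a paired change. With 20 independent null candidates, about 65% of simulated studies show at least one significant change, with a median best standardised change of 0.61.

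**4. Correlated candidates.** EEG features overlap. At K = 20 the chance falls to about 44% with pairwise correlation 0.5, and to about 23–25% with 0.8. The lowest of these is still more than four times the nominal 5% (23/5 = 4.6).

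**5. What a lock would achieve.** In a simulation, the best of 20 null candidates was picked by its correlation in one phase and then tested in the other phase of the same 15 patients. The nominal rate of false confirmation in the same direction is 2.5%.

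| Between-phase ICC (assumed) | False confirmation |
|---|---|
| 0 | 2.3% |
| 0.3 | 3.7% |
| 0.5 | 6.0% |
| 0.8 | 22% |

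Separating the phases helps greatly when patients' values are not very stable, and less when they are. The table describes a correlation repeated in the second phase. What remains for a test of the CPAP change depends on how that change is analysed.

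**6. Trained models.** Section 1.5 plans two PSGs per patient after implantation, so there are at most 2 × 15 = 30 concomitant nights. The article does not say how these are divided between training and testing.

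**The case against.** **Declared scope.** Section 2.7 calls the study exploratory and Section 1.3 a proof of concept. The abstract and Section 1.4 speak of preliminary validation, and Section 1.4 offers any marker to later confirmatory trials. This stands, and it limits the severity. It does not cover the experimental objective, where the claim of clinical validation carries no qualifier. The deferral in Section 5 concerns vigilance, decision-making and driving, not the CPAP comparison.

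**Circularity is not established.** A reader might infer that a marker will respond to CPAP by construction. The article does not support that. No section says that CPAP response is used to select candidates. Section 1.4 separates the explorative from the experimental objective, and its sentence on recording in both periods describes data collection. The fair criticism is that the order of selection and testing is not fixed.

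**The models.** A reader might also infer that one classifier is trained and validated on the same nights. The article describes two tasks: a detector of short transitions (Section 1.6) and sleep/wake classification (Section 1.4). It does not say that training and test recordings coincide. Fold structure is commonly left to a full plan, so its absence is not an error in itself.

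**The arithmetic.** The illustration uses one value per patient. It does not represent the weekly ESS, the daily diary, or up to 4 × 28 = 112 prompted KSS and PVT assessments per patient (Section 2.4.5). The critical |r| of 0.514 does not apply to within-person analyses of those data. Candidates are not all noise either: Section 2.9.3 cites earlier evidence for microsleep. These limits stand. The figures show how large the problem can be and do not predict this study's error rate.

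**Conclusion.** The concern holds in a limited form. The documented conflict is between a data-dependent, unlimited search (Section 2.7) and an unqualified claim of clinical validation in the same 15 patients (Section 1.4), with no rule that keeps CPAP-phase data out of the selection. This leaves the validation open to selection bias; it does not show that the validation is circular.

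If there were no true effect, a chance finding at p<0.05 would occur in about 40% of studies with 10 independent candidates and 64% with 20, or about 23–44% with 20 candidates correlated at 0.8 to 0.5. These figures rest on an assumed K and one value per patient. Severity: should-fix.

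**What to change.** - Select candidate markers, thresholds and the detector operating point on pre-CPAP data only.
- Record a dated lock of a short list, ideally one lead marker and one contrast, before CPAP-phase EEG is analysed. This order matters because looking at the CPAP phase cannot be undone.
- Test the locked list on the CPAP change and on CPAP usage. Report how many candidates were tried, and label everything else hypothesis-generating.
- In Section 1.4, change *clinically validate* to *preliminarily validate*, and leave confirmation to an independent cohort. The lock reduces the bias but does not remove it, because the patients are the same and the pre-CPAP data enter the contrast.
- For models trained or fine-tuned on the concomitant PSGs, treat the transition detector and the sleep/wake classifier separately. Report performance on held-out participants, with all tuning inside the fold.

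The cost is some wording, a lock date and slightly less data for feature selection. No new data are needed.
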